## 6.3 Selection and enrollment of Subjects

### 6.3.1 Advertisement

Advertisement will be focus on the following strategies:

- Webbsites: Place trial information on 3 different websites, including clinical trials.gov, Research Match, and Fox Trial Finder website.
- UTHealth Patients: we will leverage electronic health records and electronic databases from UTHealth to reach possible candidates. We will also contact our study subjects from previous studies.
- Clinic and Hospital outreach: Informational flyers will be placed in the waiting room of the movement disorders and general neurology clinics at UTHealth (TMC, Woodlands and Harris Health Smith clinic).
- Inform Colleagues: The PI will send an email to all the neurologists at UTHealth, Baylor College of Medicine, St Luke's and Methodist. This email will include a short description of the study and the set of materials designed for physicians.
- Out-Reach to the Community: Flyers will be distributed at different events for patients, including the ones organized by HAPS and other support groups.

### 6.3.2 Pre-screening:

After contacting potential candidates and getting their approval, we will send them a pre-screening questionnaire (CPHS approved) to answer and return via a pre-paid envelope. The questionnaire provides information on the patient's diagnosis, their response to medicines, laboratory tests (no older than a year), neuroimaging results, and their current medical history. This will allow us to develop a list of appropriate candidates to screen, maximizing our recruiting time, and reducing screen failures. We will contact the responders via email or phone one month after receiving the questionnaires to inform them of a decision to consider them as potential participants in the study. If a patient is considered a good candidate, a copy of the consent will be emailed to them, and a week later, the research coordinator will contact the patient to have an initial discussion about the consent. Afterward, a screening visit will be scheduled in which a longer and more in-depth discussion of the consent would take place before starting any study procedures.

## 6.4 Estimated number of Subjects

Our goal is to recruit and retain 45 patients, with each patient finishing the one-year follow-up after the last injection and complete the study. In order to achieve this goal, we estimate the need to recruit 50 patients, which assumes a 10% projected screen failure rate.

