## 6.5 Method of Assigning Subjects to Study Drug

Subjects will be assigned to any of the three treatment arms randomly on ratio 1:1:1 by computer table randomization method to yield a total of up to 45 randomized treated subjects; 15 subjects per arm. Screen failures or subjects who exit the study prior to the administration of the first treatment dose may be replaced with additional subjects, which could cause an overall number of subjects randomized to be greater than the 45 anticipated. However, no more than 45 subjects will be treated.

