### 13.3 Screen Failures

Screen Failures are defined as any patient who has been consented but fails to continue to meet inclusion/exclusion criteria prior to the MSCs infusion. Any patient that discontinues the study subsequent to the infusion will be a study patient withdrawal.

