## 14.2 Sample Size:

Having demonstrated the safety of MSC Therapy in a previous study, sample size justification will focus on Hypothesis 1.1. Schulman et al define small, medium, and large clinically important differences on the UPDRS- Motor-as 2.5, 5.2, and 10.8 points respectively. These correspond to Cohen's  $d = 0.19, 0.39$  and  $0.81$  respectively. Current estimates assume  $N = 45$  participants randomized in 1:1:1 fashion to three conditions and a medium effect size (M-UPDRS difference = 5.2). We stipulate that relative to placebo if any treatment has a posterior probability  $> 0.70$  of conferring improvement (MDS-UPDRS-M difference  $> 0$ ) and a median posterior estimate of the effect size at least as large as an MDS-UPDRS-M difference of 2.5 (i.e. a small effect), that this treatment is eligible for continued investigation in a larger clinical trial. Under these assumptions,  $M = 1000$  Monte Carlo simulations using the normal approximation to the posterior distribution indicate that the proposed design will identify an effect of treatment 72% of the time.

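### Section 6.4's route from 50 recruits to 45 completers allows for screen failure only; with treatment capped at 45 and replacement only before the first dose, the goal requires no loss at all after dosing

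*Protocol*

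**What the plan says.** Section 6.4 sets a completer target: "Our goal is to recruit and retain 45 patients, with each patient finishing the one-year follow-up after the last injection and complete the study". It then derives the recruitment number: "we estimate the need to recruit 50 patients, which assumes a 10% projected screen failure rate".

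Section 6.5 randomises 1:1:1 "to yield a total of up to 45 randomized treated subjects; 15 subjects per arm". On replacement it says "Screen failures or subjects who exit the study prior to the administration of the first treatment dose may be replaced with additional subjects", and it closes with "However, no more than 45 subjects will be treated".

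Section 13.3 separates the two kinds of loss. Screen failure means a consented patient who stops meeting the criteria before the infusion. After that point, "Any patient that discontinues the study subsequent to the infusion will be a study patient withdrawal". Section 13.1 lets subjects withdraw at any time and lists adverse events and loss to follow-up among the reasons for ending participation. Section 13.2 gives a procedure for patients who cannot be reached. Neither gives an expected rate.

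Section 14.2 assumes N = 45 and a difference of 5.2 points, and reports that "the proposed design will identify an effect of treatment 72% of the time". Section 14.3 places the hypothesis concerned (1.1) at week 62.

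**The concern.** Section 6.4 presents 50 as the number needed for 45 patients to finish. Its only allowance is for people who never receive an infusion. The next section then closes both routes by which a later loss could be made good: no replacement is provided for once a patient has been dosed, and the number treated cannot exceed 45. The protocol thus states a final size that its own rules allow only in the best case, while elsewhere it plans for patients leaving.

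At stake is the number that readers, the monitoring board and the funder will take as the expected size at the end of the study. It also matters for section 14.2, whose probability is stated for the full 45 with no loss shown.

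**Working it through.** **1. Recruitment arithmetic.** Inputs: 45 completers, 50 recruits, 10% screen failure (6.4).

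45 / (1 − 0.10) = 50, and 50 × 0.90 = 45. The printed figure reproduces exactly, and nothing remains for loss after dosing.

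**2. Can the goal survive a later loss?** Treated patients number at most 45 (6.5), so completers = 45 − post-dose losses. The goal needs zero losses from week 0 to week 88 (last infusion at week 36, plus 52 weeks). Exits before the first dose, including any around the baseline lumbar puncture, can be replaced and do not count.

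**3. How likely is zero loss?** No rate is given, so this is an assumed range. With an independent risk d per treated patient, P(all 45 complete) = (1 − d)^45:

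| Assumed loss d | P(45 completers) | Expected completers, 45 × (1 − d) |
|---|---|---|
| 2% | 0.98^45 = 40% | 44.1 |
| 5% | 0.95^45 = 9.9% | 42.8 |
| 10% | 0.90^45 = 0.9% | 40.5 |
| 20% | 0.80^45 = 0.004% | 36.0 |

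Keeping 45 completers would take 45 / (1 − d) treated patients: 48 at 5%, 50 at 10% and 57 at 20%, all above the cap.

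**4. The 72%.** Inputs from 14.2: difference 5.2, corresponding to d = 0.39, so SD = 5.2 / 0.39 = 13.33; 15 per arm; a treatment passes if the posterior probability of improvement exceeds 0.70 and the posterior median is at least 2.5. Assumption: flat prior with the normal approximation.

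- SE = 13.33 × √(2/n)
- cut = max(2.5, 0.524 × SE)
- P(one arm passes) = 1 − Φ((cut − 5.2) / SE)

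At n = 15: SE = 4.869, cut = 2.553, P = 1 − Φ(−0.544) = 70.7%. The printed 72% rests on 1,000 simulations, so its Monte Carlo standard error is √(0.72 × 0.28 / 1000) = 1.4 points; the figure reproduces within that error.

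Section 14.2 words its rule for any treatment that passes, and section 14.3 asks for at least one active group. The second result column therefore counts success if either arm passes when only one is effective. It uses the same cut and SE, with a correlation of 0.5 between the two estimates because they share the placebo arm.

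| Assumed loss by week 62 | n per arm | Cut | One arm vs placebo | Either arm, one effective |
|---|---|---|---|---|
| 0% | 15 | 2.55 | 70.7% | 73.9% |
| 10% | 13.5 | 2.69 | 68.8% | 72.3% |
| 20% | 12 | 2.85 | 66.7% | 70.6% |

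The last column can move by about 0.1 point if simulated. The fall is 1.9 and 4.0 points on the first reading, and 1.6 and 3.3 on the second. If both arms were effective, the chance that either passes at 15 per arm would be about 85%, which does not match the printed figure.

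**The case against.** **The 45 is a goal and the 50 an estimate.** True, but section 6.4 derives the 50 expressly as what the goal requires, and the derivation omits a loss that the protocol provides for elsewhere.

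**The 10% may have been meant as overall attrition.** Even so, 50 patients would have to be treated for 45 to remain after a 10% loss, and section 6.5 forbids treating more than 45.

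**The analysis plan will deal with missing data.** It may, and its silence here is no fault. But no analysis method creates room in 50 × 0.90 or lifts the cap.

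**A patient who leaves is not wholly lost to the analysis.** This stands. Section 13.1 encourages an early termination visit, the study schedule includes the OFF motor score there, and motor scores are also taken at weeks 9, 27 and 40. The percentages above treat every leaver as contributing nothing, so they are a pessimistic case.

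**The effect on the 72% is small.** This also stands. A 10% loss costs about 2 points against a Monte Carlo standard error of 1.4.

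A reader might go further and infer that the 72% itself holds only with no drop-out over 88 weeks. The protocol does not support that. The probability concerns week 62, so later losses do not touch it. And if either arm may pass with one effective, the calculation still gives 72.3% after a 10% loss. N = 45 is the stated input, but the printed figure is not shown to depend on every one of the 45.

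**Conclusion.** The defect in section 6.4 is firm and needs no outside figure: the recruitment arithmetic, the cap and the replacement rule together mean that 45 completers can be reached only with zero loss after dosing. How unlikely that is depends on an assumed rate: about a 10% chance at 5% loss per patient and about 1% at 10%, taking losses as independent.

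The consequence for section 14.2 is secondary. Its probability is stated at N = 45 without any loss shown. Assumed losses of 10% to 20% by week 62 would lower it by about 2 to 4 points, given an SD of 13.33, a flat prior and complete-case loss. That does not make the trial underpowered by its own standard, and it gives no ground for writing a particular replacement percentage into the protocol, because the protocol does not say whether success means one given arm or either arm. Correction is worthwhile because the stated size is wrong as written and cheap to put right.

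**What to change.** Keep 45 treated patients and recruit no more.

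- **Section 6.4:** state that the 50 covers screen failures only and that 45 is the number treated, not the number completing. Give an assumed post-dose loss, and from it the expected number evaluable at week 62 and completing at week 88. For illustration, a 10% loss by a given visit leaves about 40 of 45 there.
- **Section 14.2:** rerun the sponsor's own simulation at the expected week-62 number and report the result beside the 72%. Say whether success means that one named arm passes or that either arm does. The percentages in this review should not be copied in, since they depend on that choice and on complete-case loss.

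The cost is a few sentences and one simulation run. The stated figures become slightly less favourable. No dose, visit or clinical rule changes.

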## 6.5 Method of Assigning Subjects to Study Drug

Subjects will be assigned to any of the three treatment arms randomly on ratio 1:1:1 by computer table randomization method to yield a total of up to 45 randomized treated subjects; 15 subjects per arm. Screen failures or subjects who exit the study prior to the administration of the first treatment dose may be replaced with additional subjects, which could cause an overall number of subjects randomized to be greater than the 45 anticipated. However, no more than 45 subjects will be treated.

## 7. Study intervention: Mesenchymal stem cell therapy

### 7.1 Allogeneic mesenchymal stem cells

Bone marrow extraction from a healthy donor (21 CFR Parts 1271 Subpart C) will be obtained by aspiration under local anesthesia at Memorial Hermann Hospital. Testing will be performed using FDA-approved licensed kits by Gulf Coast Regional Blood Center within seven days of collection of the marrow. Mesenchymal stem cells will be expanded 4 passages using a Terumo Quantum Bioreactor by the Center for Cell and Gene Therapy of Baylor College of Medicine under Current Good Manufacturing Practices designated by the FDA. Thawing will be initiated on the planned date of administration, the cells will go through the tests described in the manufacturing section and will be placed in 5% buminat Fenwal transfer packs routinely used in blood banks. Bags will be covered with an opaque cloth, so differences in the contents cannot be appreciated. The concentration of the infusion will be  $1.5 \times 10^7$ /ml. The cells will be transported from the CAGT laboratory to the Memorial Hermann hospital clinical research unit (CRU) in certified coolers at 4°C-10° C, this is an approximately 15 minutes transport that via routes that link the Texas Medical Center institutions. Upon receipt, the cell packs will be examined for integrity and appearance, and this will be documented on the administrative paperwork. *(For a sample of labeling see Appendix D).*

### 7.2 Placebo

Placebo will be identical to the investigational product but will not contain MSCs. Placebo will be constituted by a 5% buminat solution. All bags will be covered with an opaque cloth, so differences in the contents cannot be appreciated.

### 7.3 Delivery route and infusion rate

A study drug or placebo will be supplied to each one of the patients as an intravenous infusion. Antecubital vein access will be used for the infusion with 18 or 20 gauge catheter tubing. The access will be initially primed with normal saline; thereafter the study drug will be infused at a rate of 2 ml/min followed by a flush with 25ml of normal saline. This rate may be modified dependent on the patient's response. *(As detailed in Section 11.1.2)*

### 7.4 Facility: Clinical Research Unit

The infusion will take place in the clinical research unit (CRU) located on the third floor, Robertson Pavilion 352 at the Hermann Memorial Hospital in the Texas Medical Center. This facility provides a team of research nurses, study coordinators, and lab specialists. Their services include outpatient and inpatient rooms, diagnostic tests and procedures, regulatory monitoring, critical or emergent response access, and lab services 24 hours a day.

## 8. Study assessments

### 8.1 Demographics and complete medical history

Subjects will provide information on their demographics, complete medical history including social, smoking, alcohol and caffeine usage, as well as concomitant prescribed or OTC medication usage including date started, dose, and frequency. *(See Appendix E for the medication form)*

#### Allowed Concomitant Medications

Provided they were in use for at least 60 days prior to infusion, a stable regimen of central nervous system acting medications is allowed. These include benzodiazepines, antidepressants, hypnotics, anti-psychotic, and dopaminergic therapy (all levodopa formulations, dopamine agonists, amantadine, anticholinergic agents, and MAO-B inhibitors). Any modifications to the medical regimen will be determined by the PI.

#### Medications or Supplements Not Allowed

The regular use of over the counter medications other than a standard daily multivitamin, pain medication, antihistamines, and cold medications or any experimental medication is not allowed.

### 8.2 Vital signs, orthostatic changes, weight and height

Blood pressure (supine and standing), heart rate (supine and standing), respiration, oxygen saturation, and body weight (in kg) will be measured during most of the visits. Height (in cm) will be measured at the screening visit only.

### 8.3 Physical and neurological examination

A complete physical and neurological examination will be performed and recorded at every clinical visit. The neurologic exam will include orientation to self, time and place, speech observation, cranial nerves, Global Bradykinesia, dexterity, tremor, muscle tone, strength, sensory, reflexes, cerebellar function, Retropulsive pull test, Romberg's test, and tandem gait.

### 8.4 Laboratory Test

- Complete blood count (CBC) with differential: hematocrit, hemoglobin, platelet count, RBC indices, Total RBC, Total WBC, and WBC & differential. Additionally, for CSF analysis protein and glucose.
- Comprehensive Metabolic Panel: albumin, total protein, Alkaline phosphatase (ALP), Alanine aminotransferase (ALT), Aspartate aminotransferase (AST), Blood urea nitrogen (BUN), Calcium, Carbon dioxide, Chloride, Creatinine, Glucose, Potassium, Sodium, Total bilirubin
- Specialty Blood Chemistry: INR, PT, PTT, and dipstick urinalysis.

### 8.5 Rating scales

#### 8.5.1 MDS-UPDRS (Movement Disorder Society Unified Parkinson's disease Rating Scale)

The MDS-UPDRS serves as a disability and impairment scale for progression; it is divided into four sections:

- Part I: Non-Motor Aspects of Experiences of Daily Living (13 questions).
- Part II: Motor Aspects of Experiences of Daily Living (M-EDL) (13 questions).
- Part III: Motor examination (18 questions total, 9 of those with bilateral assessment of different body).
- Part IV: Motor complications (6 questions).

All items have 5 response options with uniform anchors of: 0 = normal, 1 = slight (symptoms/signs with sufficiently low frequency or intensity to cause no impact on function), 2 = mild (symptoms/signs of frequency or intensity sufficient to cause a modest impact on function, 3 = moderate (symptoms/signs sufficiently frequent or intense to impact considerably, but not prevent function), 4 = severe (symptoms/signs that prevent function).

The motor section of the MDS- UPDRS will be performed by a qualified Movement Disorder Specialist.

#### 8.5.2 Modified H&Y (Hoehn and Yahr scale)

The Modified Hoehn and Yahr Scale is a staging instrument that defines 8 broad categories of motor function in Parkinson's disease, starting at Stage 0: no signs of disease to the highest stage 5: wheelchair bound or bedridden unless aided. The principal investigator will conduct the assessment at each clinical visit (See Appendix B for a copy of the Modified Hoehn and Yahr Scale).

### 8.5.3 TUG (Timed Up and Go Test)

Time in seconds required to stand from a chair, walk 7m, turn, walk back to the chair and sit down. The principal investigator will conduct the assessment at each clinical visit.

### 8.5.4 ADL (Modified Schwab and England Activities of daily living score)

The Schwab & England scale is a physician assessment of the subject's level of independence. The subject will be scored on a percentage scale reflective of his/her ability to perform acts of daily living in relation to what he/she did before Parkinson's disease appeared. Scores range from 0% to 100% in increments of 10%, where 100% is completely independent and 0% is only vegetative functions. The principal investigator will conduct the assessment at each clinical visit (See Appendix F for a copy of the ADL).

### 8.5.5 PDQ-39 (Parkinson's Disease Questionnaire)

The PDQ-39 is a 39 questions Parkinson's disease self-completed that assess Parkinson's disease-specific health related quality over the last month. Thirty nine multiple-choice items covering 8 dimensions: mobility (10 items), activities of daily living (6 items), emotional well-being (6 items), stigma (4 items), social support (3 items), cognition (4 items), communication (3 items) and bodily discomfort (3 items). All items are assumed to impact QoL and must be answered to compute scores for each dimension. Questions are answered based on experiences from the preceding month using a 5-point ordinal scoring system: 0 = never, 1 = occasionally, 2 = sometimes, 3 = often, 4 = always. Lower scores reflect better quality of life.

Dimension score = sum of scores of each item in the dimension divided by the maximum possible score of all the items in the dimension, multiplied by 100. Each score range from 0 = never have difficulty to 100 = always have difficulty his calculation provides a percentage score ranging between 0 and 100. Overall score can be summarized as the Parkinson's Disease Summary Index (PDSI). PDSI sum of dimension total scores divided by 8. This calculation provides a percentage score ranging between 0 and 100. The higher the percentage, the higher the disease impact on the quality of life. (See Appendix G for a copy of the PDQ-39).

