  - Quality of life: based on changes in the modified Schwab and England activities of daily living scale (ADL), Parkinson's Disease Questionnaire 39 (PDQ-39) and EuroQol- 5 Dimension (EQ-5D) from screening and at the final visit. The normal progression is an annual change of 10% in ADL and a change of less than 10% of the PDQ-39 at the final visit compared with the screening visit. Therefore a change of > 10% in ADL or the PDQ-39 over the 1 year study period will be considered clinically significant. For the EuroQol- 5 Dimension (EQ-5D), simulation-based estimates defined the minimally important difference (MID) index score to be between 0.037 and 0.069.
  - Non-motor symptoms: The non-motor symptoms questionnaire (NMS) and The University of Pennsylvania Smell Identification Test (UPSIT- 40 odor test booklet).
  - Cognitive function: measured by the change in Montreal Cognitive Assessment (MoCA) from screening to final visit. Normal change is less than 3 points per year. Therefore a  $\geq 3$  point change over a one year study will be considered clinically significant.
  - Behavioral changes: The Columbia Suicide Severity Rating Scale (C-SSRS), Geriatric Depression Scale-Short Form (GDS-SF), and Parkinson Anxiety Scale (PAS). Suicidal ideation will be assessed by the Columbia Suicide Severity Rating Scale (C-SSRS); any

positive response to any of the questions will be considered significant and would require further investigation. A score of 8 or more in the Geriatric Depression Scale will be considered significant and would require further investigation.

3. Explore putative mechanisms of action for the effect of MSC therapy. We will assess the putative paracrine mechanism of MSCs using neuroimaging and measuring concentrations of cytokines, chemokines, growth factors, neurotransmitters and alpha-synuclein oligomers in the blood (serum or plasma) and CSF.
  - Neuroimaging: 3 imaging time points per patient, baseline, week 40, and week 88.
    - Perfusion MRI: We will measure resting cerebral blood flow (CBF) using a pseudo-continuous arterial spin labeling (pCASL) MRI sequence with gradient-echo echo-planar imaging (EPI). Recent ASL studies of PD patients report wide-spread cortical hypoperfusion and, subcortically, hypoperfusion of the caudate nucleus.

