| 23 | Felt you had to conceal your Parkinson's from people?                  |  |  |  |  |          |
| 24 | Avoided situations which involve eating or drinking in public?         |  |  |  |  |          |
| 25 | Felt embarrassed in public due to having Parkinson's disease?          |  |  |  |  |          |
| 26 | Felt worried by other people's reaction to you?                        |  |  |  |  |          |
| 27 | Had problems with your close personal relationships?                   |  |  |  |  |          |
| 28 | Lacked support in the ways you need from your spouse or partner?       |  |  |  |  |          |
|    | If you do not have a spouse or partner tick here                |                          |  |                          |                          |                                  |
| 29 | Lacked support in the ways you need from your family or close friends? |  |  |  |  |          |

*Please check that you have ticked **one box for each question** before going on to the next page*

**Due to having Parkinson's disease,  
how often during the last month  
have you....**

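### PDQ-39 scoring in section 8.5.5 has no rule for the unscored no-partner box at item 28, so a patient who uses only that box gets no social-support score and no summary index

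*Protocol*

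**What the plan says.** Section 8.5.5 of the protocol sets out the PDQ-39 scoring in four parts.

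- Completeness: "All items are assumed to impact QoL and must be answered to compute scores for each dimension".
- Item scores: "0 = never, 1 = occasionally, 2 = sometimes, 3 = often, 4 = always". There is no code for an item that does not apply.
- Formula for each dimension: "sum of scores of each item in the dimension divided by the maximum possible score of all the items in the dimension, multiplied by 100".
- Summary index: "PDSI sum of dimension total scores divided by 8".

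The same section gives social support three items.

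The form in Appendix G asks at item 28 how often the patient has "Lacked support in the ways you need from your spouse or partner". Beneath it stands one extra box: "If you do not have a spouse or partner tick here". The protocol does not give that tick a score, remove the item from the denominator, or allow an index from fewer than eight dimensions. Sections 6 to 6.2 do not make partner status a condition of entry.

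Section 5.1.2 names the PDQ-39 among the quality-of-life outcomes. It treats as normal progression "a change of less than 10% of the PDQ-39 at the final visit compared with the screening visit", and a larger change as clinically significant. Quality of life is modelled under Hypothesis 2.2 at the final analysis (14.3) and the interim analysis (14.4).

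**The concern.** The scoring rule and the form it is meant to score do not fit together. A patient without a partner who fills in the form as printed gives 38 scored answers and one tick with no value. The completeness rule then blocks the dimension that contains item 28, and the fixed divisor of 8 blocks the index. The cause is a largely stable personal circumstance, so the gap would usually recur at every scheduled PDQ-39 assessment: screening and weeks 9, 27, 40, 62 and 88.

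At stake is how many patients contribute to a secondary outcome in arms of 15. If the rule is followed, those patients drop out of the index. If it is not, someone must improvise a score, and the most obvious choice (item 28 = 0) distorts the scale. The protocol is not merely silent here: it fixes a rule that its own appendix prevents some patients from meeting.

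**Working it through.** **Inputs.** From section 8.5.5: dimension sizes 10, 6, 6, 4, 3, 4, 3, 3; item scores 0-4; dimension score = sum / maximum x 100; index = sum of dimension scores / 8. From section 6.5: 45 patients, 15 per arm. The share without a partner is not in the protocol; 10-40% is assumed for illustration.

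**The stated structure reproduces.** 10 + 6 + 6 + 4 + 3 + 4 + 3 + 3 = 39 items in 8 dimensions. With every item at 4, each dimension is 100 and the index is 800 / 8 = 100, as the protocol says.

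**Where item 28 falls.** The first four dimensions take 10 + 6 + 6 + 4 = 26 items. Counting in the listed order, social support is therefore items 27-29, with a maximum of 3 x 4 = 12. The protocol does not print this mapping, but the loss of the index does not depend on it, because the index needs all eight dimensions wherever item 28 sits.

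**Literal application.** Box ticked, no 0-4 answer: 2 of 3 social-support items are scored, so that dimension has no score. Only 7 of the 8 terms of the index exist, so there is no index. The other seven dimension scores can be computed.

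**Loss of precision.** If a share p is lost equally in each arm, and the outcome variance is unchanged, the standard error of an arm contrast is multiplied by 1/sqrt(1 - p).

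| p (assumed) | Without index, of 45 | Per arm of 15 | Factor on standard error |
|---|---|---|---|
| 10% | 4.5 | 1.5 | 1/sqrt(0.9) = 1.05 |
| 20% | 9 | 3 | 1/sqrt(0.8) = 1.12 |
| 30% | 13.5 | 4.5 | 1/sqrt(0.7) = 1.20 |
| 40% | 18 | 6 | 1/sqrt(0.6) = 1.29 |

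**The workaround of scoring item 28 as 0 over 12.** The highest possible social-support score becomes 8 / 12 x 100 = 66.7, and the highest index (700 + 66.7) / 8 = 95.8. Both contradict the stated 0-100 range.

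The outcome is a change from screening, so error in change matters most. Suppose items 27 and 29 each move by one category:

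- denominator 12: 2 / 12 x 100 = 16.7 points of social support;
- denominator 8 (the two applicable items): 2 / 8 x 100 = 25 points;
- difference in the index: (25 - 16.7) / 8 = about 1.0 point.

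The ratio 8 / 12 is constant, so every change in social support for such a patient shrinks by one third.

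**The case against.** **The form does not tell anyone to leave item 28 out.** It says to tick a box, under a general instruction to tick one box per question. A patient without a partner might mark a 0-4 answer as well, and would then be scored. This stands: the loss applies to those who use only the box, and it would be wrong to say that the index is lost for every patient without a partner.

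**The denominator could be read as 8 when item 28 does not apply, and a scoring detail may sit in a statistical analysis plan that is not shown.** This is possible. Even so, the completeness sentence in 8.5.5 would still forbid the score, so the later document would have to depart from the protocol.

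**A reader might infer that the rule biases the treatment comparison, because it removes a distinct subgroup.** The documents do not support that. Partner status at screening precedes randomisation and the same rule applies in every arm. Excluding on such a trait costs precision and narrows the population described; it does not in itself bias the randomised contrast. A chance difference in partner status between arms would make the analysed arms unequal in size. Only a change of partner status after randomisation could tie missingness to treatment, and nothing in the protocol suggests that this would be common.

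**A reader might also quote a 2.1-point error in the index from scoring item 28 as 0.** That figure is for a patient who answers sometimes to items 27 and 29: (50 - 33.3) / 8 = 2.1. It is an error in level. If the answers are the same at both visits, the error in change is zero.

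**The reach is narrow.** Section 8.5.5 says only that the overall score can be summarised as the index, and no section makes the index the analysed variable. The Schwab and England scale and EQ-5D also measure quality of life. This stands and limits the weight of the point.

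**Conclusion.** The point holds in a limited form. The scoring rule in 8.5.5 and the form in Appendix G contradict each other. Applied as written, a patient who uses only the no-partner box has neither a social-support score nor a summary index at any PDQ-39 visit, with 38 of 39 items answered.

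The consequence is mainly lost precision and generalisability for a secondary outcome: about 4.5 to 18 of 45 patients and a standard error about 5-29% larger. Those figures rest on an assumed 10-40% without a partner, literal use of the rule, equal loss across arms and unchanged variance. The true number cannot be taken from the protocol. The primary motor outcome, its decision rule and the sample size are untouched.

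**What to change.** Amend section 8.5.5 so that, when the no spouse or partner box is ticked, social support = (item 27 + item 29) / 8 x 100 and the index is computed from all eight dimensions. The completeness sentence should carry this exception. This keeps the 0-100 range and avoids the one-third shrinkage that comes from scoring item 28 as 0.

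The cost is one sentence in the protocol and one branch in the scoring program, with no new data. The downside is one fewer item behind social support for these patients.

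How to score a patient whose partner status changes during follow-up is a separate choice. Using the two-item version at all of that patient's visits compares like with like, but it discards a validly answered item and lets a later event alter the screening score. The documents do not settle this.
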